**Method:**

This is a feasibility and acceptability single-blind pilot randomised controlled trial comparing CUES (intervention) to a brief psychoeducation, emotional literacy, and relaxation programme (enhanced services as usual). Participants will be assessed at baseline and followed-up immediately post-treatment, and at 12 and 26 weeks post-treatment. Parents who have a child with ASD and anxiety (aged 6–16 years) will be invited to take part in the study and written parental informed consent and child assent will be obtained. Participants will be recruited from the National Health Service mental health teams in the UK. Sixty participants will be randomised to either intervention or enhanced services as usual in a 1:1 ratio.

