### Setting and participants

Sixty parent participants will be recruited via NHS services (including diagnostic clinics and Child and Adolescent Mental Health Services). This number is based on recommendations for good practice in feasibility studies [35]. Parents are eligible for study entry if their child meets the following criteria: 1) a diagnosis of ASD; 2) aged 6–16 years; 3) experiences some anxiety; 4) no intellectual disability or mild-to-moderate intellectual disability; and 5) have sufficient language ability to complete appropriate outcome measures (with assistance if required).

Parents themselves will have sufficient spoken and written English to provide written informed consent, complete assessments, and participate in the intervention. Parents are not eligible for study entry if their child meets the following criteria: 1) no diagnosis of ASD diagnosis; 2) experiences severe and complex anxiety disorder (based on the clinical judgement of clinicians); 3) has severe intellectual disability; or 4) has complex health conditions.

Furthermore, children of parents who have significant mental health difficulties will not be eligible to participate.

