Parents will attend the programme, with two therapists with expertise in ASD facilitating each group. Each group will include approximately ten parents and sessions will take place weekly for 8 weeks. Each session will be 2 h in duration. ‘At home’ activities will be set each week for parents and children to complete between sessions. The programme begins with a focus on the development of understanding of uncertainty in everyday life, the nature and impact of IU, and promotes the use of strategies to flexibly manage IU across a range of settings. The intervention helps parents to recognise IU and identify potential developmental and environmental factors that may trigger IU for their child. It further teaches parents to plan and use appropriate strategies aimed at increasing their child’s tolerance of uncertainty. Each parent will be provided with weekly materials and individual support to identify strategies to address a chosen target IU situation. This target situation is the focus for parents to practise the new strategies with their child, thus ensuring that strategies are individually tailored for each child and are developmentally appropriate. The group situation provides extensive opportunities for mutual learning and support. The CUES intervention has incorporated and synthesised components of existing good practice in relation to anxiety treatment for children with ASD. It provides the opportunity for parents to develop an understanding of IU and its impact, to try out various strategies, and provides opportunities for discussion, mutual support and sharing of ideas, and experiences and strategies, importantly building parents’ knowledge and confidence to support their child at home to develop a more flexible approach to uncertainty.

Therapists delivering CUES are trained in the skills needed to deliver the programme through two training sessions (5 h in total). To ensure the intervention is being delivered as intended, with high fidelity to the manual, the principal investigator (JR) and the clinical lead (VG) will undertake supervision and monitoring of the quality of parent group sessions by video, providing timely feedback to group leaders. Weekly supervision of the therapists will be conducted by JR and VG. Treatment fidelity will be maintained and investigated from multiple standpoints, including supervisor feedback, and formally by observer ratings of recordings of the group sessions.

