#### Enhanced services as usual arm: Understanding Autism

Understanding Autism will comprise two parent group sessions. Each session will be 2 h in duration. Parent group-based interventions provide parents with the opportunity not only to develop knowledge and skills in relation to the treatment target (in this case IU), but also provide opportunities for discussion, mutual support, and sharing of ideas, a process which parents tell us they value. Given the feasibility and acceptability aims of the current study, we were concerned that offering families in the control arm no opportunity to meet together as a group might significantly bias favourable responses in relation to acceptability towards the CUES intervention arm. In addition, treatment as usual is highly variable and thus the introduction of a two-session programme for the enhanced services as usual arm enables us to provide parents with some common content, and credibility/expectancy will be rated for both arms, whereas services as usual cannot be rated; this creates a greater level of equipoise than treatment as usual. There is currently no equivalent eight-session parent support group available to parents of children with ASD within this age range, and parents in the control arm receive a two-session Understanding Autism programme. This enables parents randomised to the control arm to have experience of a parent group setting. Both arms will continue to receive treatment as usual, which will be recorded on the demographics form.

The group will focus on psychoeducation, social communication, repetitive behaviours, and making and keeping friends. There are opportunities for parents to engage in group discussion regarding their experiences, such as the ASD diagnostic process.

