### Randomisation and blinding

Participants are randomised on a 1:1 basis to receive either CUES or Understanding Autism, without stratification. Randomisation occurs online through Sealed Envelope (https://www.sealedenvelope.com/). Participants will be aware of group status due to the nature of the intervention, but the primary outcome assessor will be blind to group allocation although, despite instruction not to do so, participants could unwittingly break blindness if they reveal details about the intervention at post-treatment assessment.

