### Planned analyses

Sydes and colleagues [48], who reviewed requirements for data monitoring committees (DMCs), concluded that DMCs are recommended when trials have any of the following features: trials on high-profile topics that are a focus of community concern, that will be used to seek regulatory approval or that are likely to profoundly affect clinical practice; trials with serious safety concerns, unknown risks or that are implemented in vulnerable populations; and trials where independent monitoring is needed because of double-blind treatment assignment or long-term follow-up or because the sponsoring company does not have standard operating procedures. DMCs may not be needed: 1) for trials that are of short duration (where it may not be feasible to convene a DMC in a timely fashion to review the data); 2) for trials with known risks that are minimal; 3) for trials in which the objective is to demonstrate principles (such as in early-phase clinical trials); or 4) for trials on behavioural or administrative issues. In the current case, given the acceptability and feasibility aims where we are constantly monitoring events that could relate to acceptability and feasibility such as nonattendance (for any reason) and, if not informed of a reason, this is followed-up, coupled with the short duration, minimal risks, and the parent-delivery of treatment, it was determined that a DMC was not required. In this case, data management will be discussed at Trial Steering Committee meetings.

As this is a feasibility study, analyses will be mainly descriptive, and no interim analysis will be undertaken. Formal power calculations are not appropriate as the study is not designed to test for a difference between treatments. Feasibility will be explored by examining: 1) the number of families who consented, their attendance, and complete data at 6 months; and 2) that qualitative data support the acceptability of CUES by the majority of parents and clinicians.

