We will also undertake some preliminary analysis of treatment effects. As a randomised controlled trial, primary analysis will be based on the intention-to-treat principle with analysis based on groups allocated at randomisation and all randomised families included. The extent of missing data will be assessed. Rates will be calculated as defined and reported with 95% confidence intervals. At baseline and by group, the distribution of all variables will be examined and summarised by measures of central location and spread and reported with 95% confidence intervals. Baseline categorical variables will be tabulated and percentages reported with 95% confidence intervals. The difference in mean change for all outcome measures will be examined between the groups from baseline to each of the two time points with accompanying 95% confidence intervals. Evidence of clustering and/or contamination will be explored. Such results will be interpreted cautiously because of the size of the study and the possible imbalance in prerandomisation baseline covariates. The relationship between baseline covariates and outcome measures will be examined graphically and quantified appropriately depending on their distribution.

While no formal economic evaluation will be undertaken at this stage, questionnaires have been designed in conjunction with patient representatives which will measure resource use associated with managing IU. The data gathered from these questionnaires will provide information about healthcare resource use and personal costs to families which will aid the design of a potential future economic evaluation associated with a full trial. Numbers of families who express interest, continue to treatment, and who complete treatment will be recorded. When families do not participate/complete treatment, the reasons for this will be investigated, if appropriate and where possible, through brief telephone interviews or visits to families. The study team and the health economist will advise on the content of the interview schedule.

When appropriate, interviews will be recorded, transcribed, double-coded, and analysed using thematic analysis [49].

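### Both arms are delivered in parent groups, but the protocol does not commit to treatment-difference intervals that allow for group, and exploring clustering in about six groups cannot show that it is absent

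*Protocol article*

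**What the plan says.** Randomisation is by family: "Participants are randomised on a 1:1 basis to receive either CUES or Understanding Autism, without stratification" (Randomisation and blinding). The total is fixed in the abstract: "Sixty participants will be randomised to either intervention or enhanced services as usual in a 1:1 ratio". That is 30 families per arm.

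Delivery is by group in both arms. For CUES, "Each group will include approximately ten parents and sessions will take place weekly for 8 weeks", and "Parents will attend the programme, with two therapists with expertise in ASD facilitating each group" (Intervention arm: CUES). The same section presents mutual learning and support among group members as a strength of the format. For the control, "Understanding Autism will comprise two parent group sessions" (Enhanced services as usual arm: Understanding Autism); the size and number of control groups are not given.

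Under Planned analyses, the preliminary treatment-effect output is the between-arm difference in mean change on every outcome measure, with 95% confidence intervals. No variance method or model is named. The one sentence on grouping is "Evidence of clustering and/or contamination will be explored". Cautious interpretation is then promised, for two stated reasons: the size of the study and possible baseline imbalance. Dependence within groups is not among them. The section also states that "Formal power calculations are not appropriate as the study is not designed to test for a difference between treatments".

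**The concern.** Families who share a group share two therapists, the same sessions and each other's advice, so their outcomes may be correlated. An interval that treats all 60 families as independent is then too narrow. The authors saw the issue, since they name clustering, but the response they state is to look for it. With so few groups, looking is a weak safeguard: real clustering of a size that matters would usually go unseen.

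No hypothesis test is planned, so the intervals carry the treatment-effect message (aim 8 asks whether CUES families improve more). The Discussion says the trial's data will inform the design and sample size of a full trial. Overstated precision, or an ICC near zero taken at face value, could carry over into that design.

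**Working it through.** **Plan's own figure.** The sample size of 60 rests on good-practice advice for feasibility studies, with no effect size, SD, power or target precision behind it. There is nothing to reproduce.

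**Inputs from the protocol article.** n = 30 per arm (60, 1:1). CUES group size m about 10, so about 30/10 = 3 CUES groups.

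**Assumptions.** Control groups are also three groups of ten (size not stated). The ICC is 0 to 0.10 (none is stated). Outcomes are in SD units of the change score.

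**Step 1: unadjusted interval.** Half-width = t(0.975, 58 df) × sqrt(2/30) = 2.002 × 0.258 = 0.517 SD.

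**Step 2: standard error.** The design effect is DE = 1 + (m − 1) × ICC = 1 + 9 × ICC. With clustering in both arms the standard error should be multiplied by sqrt(DE). With clustering in CUES only, the multiplier is sqrt((DE + 1)/2). For ICC 0.05, DE = 1.45, sqrt(1.45) = 1.20 and sqrt(2.45/2) = 1.11. For ICC 0.10, DE = 1.90, sqrt(1.90) = 1.38 and sqrt(2.90/2) = 1.20.

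**Step 3: coverage of the unadjusted 95% interval.** Two-sample t interval, 40,000 simulated trials per setting.

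| Assumed ICC | Multiplier, both arms | Coverage, both arms | Multiplier, CUES only | Coverage, CUES only |
|---|---|---|---|---|
| 0 | 1.00 | 95% | 1.00 | 95% |
| 0.02 | 1.09 | 93% | 1.04 | 94% |
| 0.05 | 1.20 | 90% | 1.11 | 92% |
| 0.10 | 1.38 | 84% | 1.20 | 90% |

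With clustering in both arms, the half-width of 0.517 SD becomes 0.517 × 1.20 = 0.62 SD at ICC 0.05 and 0.517 × 1.38 = 0.71 SD at ICC 0.10.

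**Step 4: sensitivity to group size.** With groups of 5 in both arms the multiplier at ICC 0.10 is sqrt(1 + 4 × 0.10) = 1.18. With groups of 15 it is sqrt(1 + 14 × 0.10) = 1.55.

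**Step 5: what an exploration can show.** Take the F test for groups within arm, with 2 × (3 − 1) = 4 and 2 × 3 × (10 − 1) = 54 df and a 5% critical value of 2.54. The observed F is distributed as a central F multiplied by (1 + 9 × ICC)/(1 − ICC).

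- ICC 0.05: factor 1.45/0.95 = 1.53. Power is 17%. The ICC estimate is zero or negative in 37% of trials, and its 95% sampling range is about −0.09 to 0.27.
- ICC 0.10: factor 1.90/0.90 = 2.11. Power is 32%. The ICC estimate is zero or negative in 25% of trials.

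**The case against.** The strongest reply has four parts.

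- **The method is not stated.** A reader might infer that the intervals are unadjusted and will be too narrow. The article does not say so: it names no variance method, and the detail may sit in an analysis plan that is not shown. The shortfall also needs an ICC above 0, and none is given; at ICC 0 coverage is 95%. This stands, and the point is therefore conditional.
- **No decision rule is written.** A reader might also infer that a null exploration would license intervals that ignore group. The document links the exploration to nothing. This stands. The power figures show only that the exploration cannot settle the matter, not that a flawed two-stage procedure is planned.
- **The stakes are modest.** The effect analysis is called preliminary, analyses are mainly descriptive, and caution is promised. Nor does the article say that these intervals, or an ICC from this trial, will set the full trial's sample size. This limits the consequence without removing it: caution for size and imbalance does not widen an interval, and informing the sample size is a stated purpose.
- **A model-based remedy is debatable.** A random group effect estimated from six groups meets the same lack of information. With about 4 df the t multiplier rises from 2.00 to 2.78, so intervals are about 39% wider (2.78/2.00 = 1.39) even at ICC 0. This stands, and it is why the fix below does not depend on such a model.

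Equal clustering in both arms is also only an assumption, since CUES has eight sessions and the control two. The CUES-only columns address that.

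**Conclusion.** The point holds in conditional form. The protocol recognises clustering, but its only stated response is an exploration that about six groups cannot make conclusive, and it does not commit to intervals that allow for group. If the intervals are unadjusted and the ICC is positive, they overstate precision. At an ICC of 0.10, the top of the assumed range, the true standard error is 38% larger than the unadjusted one with clustering in both arms, or 20% larger with clustering in CUES only; at ICC 0 there is no shortfall. These sizes rest on three groups of ten per arm and on an assumed ICC.

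This is worth correcting, but it does not threaten the trial's feasibility and acceptability aims.

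**What to change.** State in the analysis section that, whatever the exploration shows, each unadjusted treatment-difference interval will be accompanied by intervals with the standard error multiplied by sqrt(1 + (m − 1) × ICC) at stated assumed ICCs, for example 0.02, 0.05 and 0.10. Give these for clustering in both arms and for clustering in CUES only; with equal arms the latter multiplier is sqrt((DE + 1)/2). Use the group sizes actually formed, including those in the control arm.

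Report the estimated ICC with its confidence interval, and state that the full trial's ICC will not be taken from this trial's point estimate alone. A random group effect with small-sample degrees of freedom may be added but is optional.

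The cost is wider intervals and a little extra analysis. Each family's group has to be known, which exploring clustering already requires. Randomisation, recruitment and delivery are unchanged.

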### Dissemination plan

Dissemination of the findings will be undertaken in a number of ways. Co-applicants representing the autism community (DG and MO) will review the findings alongside the Patient and Public Involvement group and other members of the research team and assist with “translating” the main findings and implications for dissemination; a film will be made about the findings and posted on research group websites with links distributed during dissemination events. A series of reports will be written in an accessible and inclusive manner for a lay audience, including reports and newsletters for autistic people and their families, professionals and commissioners, and other agencies. Some versions will be prepared using ‘easyread’ to maximise accessibility and will be available in both written and video format. A feedback event will be hosted to present findings to families. Findings will be presented at academic meetings and written up for open-access peer-reviewed journals. UK multidisciplinary team clinicians will be informed through presentations at relevant professional meetings and conferences. Articles will be written for the professional organisations’ newsletters.

## Discussion

Anxiety affects approximately 50% of children with ASD. It significantly impacts on the everyday life of families and is a major risk factor for mental health difficulties, including suicide, in adulthood. There is evidence to suggest that IU plays a central role in the relationship between ASD and anxiety (e.g. [11]). CUES aims to target IU by providing parents with strategies to manage children’s IU and improve their everyday functioning. Therefore, CUES has the potential to improve psychological outcomes for children with ASD and their families because it provides parents with strategies that they can utilise with their child across a range of everyday contexts.

The present study will provide data on the acceptability of the CUES intervention as well as feasibility trial data to inform the design and sample size for a full-scale trial. In addition, qualitative data will be obtained to understand how feasible CUES may be for families based on participants’ experiences of the intervention.

## Trial status

The first participant was consented to the CUES trial on 19 June 2018. Recruitment is planned to continue until February 2019.

## Data Availability

The datasets generated and/or analysed during the current study are available from the corresponding author on reasonable request.

## Abbreviations

ASD: Autism spectrum disorder
CUES: Coping with Uncertainty in Everyday Situations
DMC: Data monitoring committee
IU: Intolerance of uncertainty
NHS: National Health Service
